## Abstract

Long working hours can negatively affect workers' health, wellbeing, and work performance. Previous trials reducing working time have found improvements in multiple aspects of wellbeing, including sleep, job satisfaction, and reduced burnout, while maintaining performance. However, the potential psychological and biological mechanisms underlying these improvements, including immune function and brain function, remain unexplored. Therefore, the aim of this study is to understand the bidirectional relationship between working patterns and physical and mental health, and how workplace performance is affected. We aim to test at least 150 working-age adults in the UK (approximately half with a working time reduction and no loss of salary, and half controls with no change in working patterns) in a 14-week trial, including a 2-week baseline period, with additional participants completing questionnaires only. The primary outcome measure is the difference in physical and mental health from baseline to the end of the trial among participants undergoing a reduction in working time, compared with the control group. Data collection is currently underway, and while the majority of employers in the working time reduction group adopt a 4-day week format, the specific change in working patterns is flexible and varies between employers according to their operational need, including a 9-day fortnight, two half-days and shorter working days. Core variables include brain structure and function, sleep, immune function, interoception (perception of bodily sensations), time use, diet, mental health, and workplace performance and engagement. Secondary outcomes include weekly monitoring of self-reported wellbeing changes to identify key inflection points and assess whether these are maintained at a 6-month follow-up. Overall, this study aims to generate highly novel multimodal data on the psychological and biological implications of working time reduction, including observed changes in health, wellbeing, and performance.

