### Recruitment

2.3

Employers have been recruited on a rolling basis between 2022 and 2026. Unlike most national cohort-based working-time-reduction trials, this protocol requires local recruitment because several core measures, including MRI scans, blood samples, and interoception measures, must be conducted in person at the University of Sussex. As only a minority of staff at each organization volunteer for in-person testing, a large pool of local employers is needed to achieve adequate sample sizes on these measures. Therefore, we prioritize organizations based near the research site, and invite them to join the trial at a time that suits their operational needs. Recruitment for both control and working time reduction participants is supported through local business newsletters, community talks by the senior researcher ([name]), public engagement events, research participation bulletins, social media posts, and word of mouth. A small number of employers participating in UK national pilots coordinated by the 4 Day Week Foundation have also opted into the protocol, alongside the national programmes.

Employers are primarily contacted through a senior decision-maker (e.g., CEO, Managing Director, or Human Resources lead), who determines whether their staff will implement working-time reduction or serve as controls. Except for one organization that contributed to both groups, all employees within a given organization are assigned to the same group. Organization leaders inform staff about the study and, where applicable, the planned reduction in working time. Staff are invited to a discovery call with the senior researcher, after which they can opt into the study and select which components they wish to complete (i.e., questionnaires only, additional remote measures, or an in-person visit). Participation in the research is voluntary and independent of eligibility to take part in time management training (see Section 2.5) and, for the working time reduction group, participating in their employer's working time reduction trial.

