In line with other working time reduction trials, we will include all participants allocated to the intervention group in the primary analyses regardless of the actual extent of their working time reduction, unless the company average reduction of working hours is < 1 h per week. In which case, their data will be excluded from the main analyses. In secondary analyses, we will investigate whether intervention effects vary by the extent of working time reduction by adding this as a moderator in the mixed-effects models. The extent of working time reduction will be calculated as the difference between participants' self-reported weekly working hours before the trial and during the trial. Working time reduction will firstly be modeled as a continuous variable (hours reduced), but we will also explore potential non-linear relationships using categorical hourly brackets. Additional secondary analyses will investigate whether other individual characteristics moderate the intervention effects, such as sex, age, and baseline score for a given measure. Each potential moderator will be evaluated separately by including the relevant interaction terms in mixed-effects models.

Due to the range of data types and the number of variables, variable-specific hypotheses and model variations (i.e., specific moderators and additional covariates) will be addressed in multiple follow-up preregistrations on the Open Science Framework (OSF). These will provide further details on each data-type analysis within the OSF project repository.

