Nonetheless, this protocol has limitations. Our measures do not capture all factors that may influence responses to working-time reduction. For example, we did not collect information about participants' caregiving responsibilities or other non-work demands, which could moderate the benefits of reduced working hours. These choices reflect the need to minimize participant burden in an already intensive multi-modal protocol by focusing on measures most relevant to the biological mechanisms under investigation, acknowledging that other trials have focused more extensively on social and economic factors (e.g., Gomes and Fontinha, 2024; Lewis et al., 2023). In addition, due to in-person testing requirements, recruitment primarily relied on small to medium employers located near the research site who self-selected into either the working-time reduction or control group. This may limit generalizability to larger or geographically diverse organizations and may also introduce selection effects, as employers with more progressive work cultures were more likely to adopt working time reduction, with considerable variability in how organizations implemented working-time reduction (e.g., fixed vs. flexible days off). It must also be acknowledged that organizations from which participants are recruited self-select into either the working time reduction or control group. Given the need to carefully plan the nature and implementation of working time reduction, randomization of group assignment is not feasible. However, this does increase the likelihood of selection bias, with baseline characteristics in work culture and organizational structure impacting group membership, an issue inherent to working time reduction trials. Therefore, it will not be possible to entirely rule out expectancy effects, that observed benefits of working time reduction are driven by participants' expected improvement over the trial period. However, inclusion of baseline periods in both groups will allow us to observe whether such effects appear before the implementation of working time reduction. Finally, given the complex nature of this protocol and the involvement of the same researchers in both the data collection and analysis processes, it is not possible to entirely blind those performing the analysis to group membership (working time reduction vs control).

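### The single slope for hours reduced mixes differences between employers with differences between colleagues, so it cannot safely be read as an individual dose-response

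*Protocol article*

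**What the plan says.** Section 3.2 (Model design) makes the extent of working time reduction a secondary analysis, done "by adding this as a moderator in the mixed-effects models". The extent is "calculated as the difference between participants' self-reported weekly working hours before the trial and during the trial". On its form: "Working time reduction will firstly be modeled as a continuous variable (hours reduced"; hourly brackets are added only to explore non-linearity. On moderators generally: "Each potential moderator will be evaluated separately by including the relevant interaction terms in mixed-effects models".

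Table 1 lists hours of reduction among the individual-level covariates. The company-level covariates are industry, size, trial start month and profit status. Organization is one of up to three random effects. The article plans no company-mean term for hours. It does refer to a company average reduction, in the rule that excludes a company whose average is below 1 hour per week.

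On where the hours come from, the Abstract says "the specific change in working patterns is flexible and varies between employers according to their operational need". Section 2.3 (Recruitment) names a senior decision-maker "who determines whether their staff will implement working-time reduction or serve as controls". Section 4 (Discussion) reports "considerable variability in how organizations implemented working-time reduction" and, as a selection effect, that "employers with more progressive work cultures were more likely to adopt working time reduction".

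**The concern.** The hours a participant gives up have two sources: the format the employer introduced, and how far that person's own hours fell under it. A comparison across employers also carries whatever else differs between those employers. A comparison between colleagues does not, because they share an employer. A random intercept for organization allows for correlated outcomes within a company, but it assumes that the company effect is unrelated to hours cut. It does not separate the two comparisons.

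At stake is the reading of the result. The Introduction cites earlier multi-country trials as showing that larger individual reductions predicted larger gains. A positive slope here would naturally be taken as confirmation, although it could arise wholly or partly because employers that cut more hours also improved for other reasons. Section 3 presents these plans as applying to all data types, so each modality would inherit the term.

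**Working it through.** The article gives no figure for this analysis: no split of the variance in hours, no number of employers, no expected slope. There is nothing to reproduce, so the check is an argument from the text followed by simulation on assumed inputs.

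**1. Does format move hours between employers?** By the definitions in Sections 1 and 2.1, a 4-day week removes 1 workday per week and a 9-day fortnight removes 1 per two weeks, or 0.5 per week. The ratio is 1 / 0.5 = 2. Assuming an 8-hour day, that is 8 h against 4 h. Two half-days remove 2 × 4 = 8 h, the same as a 4-day week. So format creates some variation between employers, but not every format differs from every other.

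**2. What one slope estimates.** For participant i in company j, write change = a + β·h_ij + u_j + e_ij, with h_ij = (company mean) + (deviation from it). The fitted β is approximately w·β_between + (1 − w)·β_within, with w between 0 and 1. If hours have no effect but u_j is correlated with the company mean, then β_within = 0 and β ≈ w·β_between, which is not zero.

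**3. Main simulation.** Change scores in the intervention arm, random-intercept REML model, no true effect of hours, 600 runs per scenario, nominal 5% test. All inputs are assumptions:
- employers × participants: 15 × 5, 25 × 3 (75 in total each) or 30 × 10 (300);
- employer share of the variance in hours: 0.2, 0.5 or 0.8;
- outcome intraclass correlation: 0.05 or 0.15;
- correlation between the employer effect and hours cut: 0, 0.5 or 0.8.

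False-positive rate of the single slope:

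| Correlation | 75 participants | 300 participants |
|---|---|---|
| 0 | 4–7% | 5–7% |
| 0.5 | 6–25% | 10–46% |
| 0.8 | 10–57% | 18–88% |

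The within-employer slope averaged close to zero and rejected in 3–7% of runs throughout. The simulation standard error at 5% is √(0.05 × 0.95 / 600) = 0.9 percentage points, so this is in line with the nominal level.

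Two scenarios show the blend (correlation 0.5, employer share 0.5, outcome ICC 0.15):
- 15 × 5: single 0.095, within 0.000, between 0.228. Implied w = 0.095 / 0.228 = 0.42. The single slope rejects in 14.5% of runs.
- 30 × 10: single 0.081, within −0.001, between 0.252. Implied w = (0.081 + 0.001) / (0.252 + 0.001) = 0.32. The single slope rejects in 27.3% of runs.

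In the larger sample the bias is slightly smaller, but the false-positive rate is higher because the standard error shrinks. More data do not cure the problem.

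**4. Second simulation, for size and precision.** Assumed: 20 employers × 5 participants; SD of hours 2.5 between and 2 within employers (between share 6.25 / 10.25 = 0.61); correlation 0.6; no true effect of hours; 400 runs.

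| Employer effect on change (SD) | Single slope, SD per 8 h | Rejects | Within slope | Rejects |
|---|---|---|---|---|
| 0.2 | 0.20 | 9.2% | 0.01 | 4.2% |
| 0.3 | 0.29 | 18.2% | 0.01 | 4.5% |
| 0.4 | 0.34 | 21.2% | −0.04 | 5.5% |

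The standard error of the within slope was 1.53 times that of the single slope (150 runs).

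**The case against.** The strongest reply is that Section 3.2 contrasts a continuous with a bracketed form and says nothing about centring, and that it leaves specific moderators and extra covariates to later preregistrations. Those preregistrations could still add the split. That stands as a reason to put the change there. It does not remove the point, because this moderator, its definition, its level and its first form are already stated.

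The second reply concerns the premises, and much of it stands. A reader might infer that work culture drives how many hours are cut. The Discussion ties culture to adopting a reduction, not to its size among adopters, and the Abstract gives operational need as the reason formats differ. A reader might also infer that employers largely set the hours. The article does not quantify this: most participants moved to a 4-day week, and the measured quantity is individual self-report that counts evening and weekend catch-up work (Section 2.8.5).

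Third, the simulations contain no covariates and no correction for multiple testing, whereas the plan has both. The Discussion also mentions job control and self-efficacy as covariates. These might absorb part of an employer effect, but none of them separates the two levels. A multiplicity correction lowers the rejection rate without removing the bias.

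Finally, the within-company slope has weaknesses of its own, which are set out under the fix as its cost.

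**Conclusion.** The point holds in a limited form. The stated model gives one slope for an exposure that varies both between and within employers, and nothing planned separates the two. Whether that slope is biased depends on whether employer characteristics that affect outcomes are related to hours cut. The self-selection acknowledged in the Discussion makes this plausible, but the article does not state it.

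The size is therefore unknown. The simulated range, from about the nominal 5% to 88%, shows what the assumptions can do and is not a forecast for this trial. If hours cut are unrelated to employer characteristics among adopters, there is no inflation.

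The documents do not support the stronger conclusion that the planned analysis will show a false dose-response, or that the main result is compromised. This is a secondary analysis, and the primary group-by-time comparison does not use the slope.

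**What to change.** In Section 3.2, and in each preregistration that takes it up, replace the single hours term with two: the company-mean reduction and each participant's deviation from that mean, each with its interaction with time. Report both slopes with confidence intervals and a test of their equality. If they differ, do not present the between-company slope as an individual dose-response.

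Take the mean over the intervention participants in the analysis, so that the deviations carry no between-company component. One organization contributed to both groups, so its controls should be left out of the mean. No new data are needed: the individual hours are collected, and a company average is already required for the below-1-hour rule.

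The cost is one derived variable, a sentence or two of text, and precision. With a standard error 1.53 times as large (assumed scenario), equal precision would need about 1.53² = 2.3 times as many participants. Employers with a single participant and people taking part independently have a deviation of zero and add nothing to the within-company slope. That slope also remains open to self-report error and to confounding by role or workload, and the report should say so.

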### Descriptive statistics and inference criteria

3.3

Descriptive statistics for each outcome variable, as well as basic demographic factors (e.g., age, sex, BMI, and socioeconomic status), and individual factors (included as covariates or moderators) will be reported. For continuous variables, this will include the mean, standard deviation, and range. For categorical variables, the raw number and percentage of the sample falling in each category will be reported.

To infer effects, the *F*-value, *p*-value (including 95% CI), and partial eta-squared effect size will be reported alongside standardized beta values and their 95% CI (i.e., parameter estimates) and intraclass correlations (ICC). An effect will be considered statistically significant if *p* < 0.05 and the corresponding 95% CI does not include zero.

## Discussion

4

In this paper, we have outlined the protocol for the Sussex 4 Day Week study, in which a comprehensive dataset is collected across 14 weeks from participants before and after a meaningful reduction in working hours, alongside a control group with no change in working hours. Measures include self-reported work performance, wellbeing, sleep, and work patterns; time-use diaries; actigraphy and sleep diaries; MRI scans; blood samples; and laboratory measures assessing perception of internal body signals. In addition to providing essential context for future analyses using this dataset, we intend this protocol to serve as a model for researchers planning working time reduction interventions or occupational health studies.

A key contribution of this multi-modal study is its integration of subjective and objective measures. While recent working time reduction studies have primarily acquired self-report data, our protocol also includes diverse biomedical measures, including functional and diffusion MRI, inflammatory markers from blood samples, and actigraphy-based sleep assessments. These measures are less susceptible to expectancy or Hawthorne effects than self-report approaches. Although, given the diverse outcome variables being measured, it will largely not be possible to directly validate subjective measures using objective measures, with the exception of sleep, for which we will have both self-reported sleep duration and actigraphy watches and interoception, where we have the self-report body perception questionnaire and in-person measurements of interoceptive accuracy and awareness. However, the presence of any effects of working time reduction for the objective measures can be used as evidence that changes on any self-report measures are not solely the product of expectancy or Hawthorne effects. To our knowledge, this is the first working-time reduction study to examine changes in brain function, actigraphy-based sleep assessments and immune-related biomarkers, offering an opportunity to identify physiological mechanisms underlying changes in wellbeing and work performance.

Furthermore, sampling wellbeing and performance questionnaires each week will shed light on how individuals accumulate or conserve resources over time. COR theory purports that resource loss is more salient than resource gain for people (Hobfoll et al., 2018). Therefore, whilst our working time reduction intervention is likely to reduce resource loss (e.g., reduce burnout) and contribute to resource gains (e.g., improving wellbeing), we expect the greater impact to be on reducing resource loss-related outcomes, in keeping with the theory. This kind of dynamic tracking of resource loss and gain over time is considered important for better understanding how resource spirals emerge and how these impact work performance and wellbeing (Sonnentag and Meier, 2024). In the context of the Job Demands-Resources model (Bakker and Demerouti, 2007; Demerouti et al., 2001), we hypothesize that reduced working hours primarily function as a resource gain, leading to improvements in employee wellbeing and organizational outcomes. Although employees may experience pressure to complete the same workload within fewer days due to potential work intensification, we expect that the additional time off work will create such resource gain that wellbeing and performance will improve overall. This expectation is supported by previous research demonstrating wellbeing improvements following working time reduction (Fan et al., 2025). We also took stable measures of job and personal resources (e.g., job control, self-efficacy) to include as covariates in statistical models, given their established relationships with wellbeing and performance outcomes (Bakker et al., 2023).

The time-use diary data enables investigation into how activities undertaken during increased non-work time relate to employees' recovery experiences, and subsequently their wellbeing and performance (Sonnentag and Fritz, 2015; Vandoros et al., 2025). Sleep duration and quality may function as an additional key pathway of recovery through which resources are replenished (Sonnentag et al., 2008; Zijlstra and Sonnentag, 2006). The fMRI analysis will allow us to test the hypothesis that adaptive changes in brain function underlie benefits to both rest and motivation ([name] and Russell, 2025). While prior work has provided limited evidence of an association between working hours and brain function (Souter et al., 2026), the intervention design used in the current project will provide additional insight into mechanisms.

This protocol also addresses several limitations common in previous trials. Firstly, data collection spans multiple years (2022–2027), with employers initiating the research protocol at different times of the year. This rolling recruitment approach helps to reduce the influence of seasonal effects that may arise when data for all participants are collected on the same schedule. For instance, the non-profit 4 Day Week Global coordinated trials in which multiple employers were studied on the same calendar timeline, with a coordinated switch date to the new schedule, and cohort-level work reorganization support (Backmann et al., 2024; Fan et al., 2025; Gomes and Fontinha, 2024).

Secondly, control groups have not always been included in working time reduction studies (e.g., Lewis et al., 2023), or have used much smaller sample sizes than working time reduction groups (e.g., Backmann et al., 2024; Fan et al., 2025), or do not receive the same organizational training that enables isolation of changes due to working time reduction specifically (e.g., Fan et al., 2025). In contrast, our study includes a balanced control group of comparable size and sector composition, whereby control organizations complete the same protocols. This includes time management training, which allows stronger causal inference by isolating the specific effects of reduced working time from changes attributable to advice on productivity and time-management principles.

Nonetheless, this protocol has limitations. Our measures do not capture all factors that may influence responses to working-time reduction. For example, we did not collect information about participants' caregiving responsibilities or other non-work demands, which could moderate the benefits of reduced working hours. These choices reflect the need to minimize participant burden in an already intensive multi-modal protocol by focusing on measures most relevant to the biological mechanisms under investigation, acknowledging that other trials have focused more extensively on social and economic factors (e.g., Gomes and Fontinha, 2024; Lewis et al., 2023). In addition, due to in-person testing requirements, recruitment primarily relied on small to medium employers located near the research site who self-selected into either the working-time reduction or control group. This may limit generalizability to larger or geographically diverse organizations and may also introduce selection effects, as employers with more progressive work cultures were more likely to adopt working time reduction, with considerable variability in how organizations implemented working-time reduction (e.g., fixed vs. flexible days off). It must also be acknowledged that organizations from which participants are recruited self-select into either the working time reduction or control group. Given the need to carefully plan the nature and implementation of working time reduction, randomization of group assignment is not feasible. However, this does increase the likelihood of selection bias, with baseline characteristics in work culture and organizational structure impacting group membership, an issue inherent to working time reduction trials. Therefore, it will not be possible to entirely rule out expectancy effects, that observed benefits of working time reduction are driven by participants' expected improvement over the trial period. However, inclusion of baseline periods in both groups will allow us to observe whether such effects appear before the implementation of working time reduction. Finally, given the complex nature of this protocol and the involvement of the same researchers in both the data collection and analysis processes, it is not possible to entirely blind those performing the analysis to group membership (working time reduction vs control).

This protocol paper will be complemented by preregistered analysis plans for each data type described above, enabling transparent and reproducible analyses as findings emerge. Taken together, this protocol provides a rigorous and transparent foundation for examining the psychological and biological effects of reduced working time, offering comprehensive multimodal evidence which will support future theory, policy, and intervention design in the fields of working time reduction and occupational health.
